##### Randomisation

Upon completion of the consent forms and Time 1 questionnaires, families will be randomised to either the intervention or CaU group. Computerized randomisation software will be used to create a randomisation table via REDCap (a secure web application for building and managing online surveys and databases) [25]. Participants will be assigned randomly to each arm ensuring a 50:50 ratio.

##### Assessments

All participants will complete consent forms and a demographic information questionnaire along with the study questionnaires through the REDCap platform. These questionnaires will be made available in English, Vietnamese, Arabic, and simplified Chinese (the four most common languages spoken in NSW). Where translated versions of questionnaires exist, they will be used, otherwise a licensed interpreter will be commissioned to translate the questionnaires during assessment. Those who cannot speak English will be linked up with services with access to interpreters as part of their service delivery. The demographic questionnaire, which will be completed at trial entry (baseline), will include the child’s date of birth, the child’s gender, whether the child was born premature, the child’s country of birth, the mother’s age, the mothers education level, the mother’s country of birth, the fathers age, fathers education level, the father’s country of birth, parent marital status, socioeconomic status, and the main language spoken in the home. The study questionnaires will be completed at three time points: baseline [Time 1], six-months post-intervention [Time 2], and 12-months post-intervention [Time 3]. See Figs. 1 and 2 for a summary of participant flow through the study.

**Fig. 1 Fig1:**
[figure not shown]
Participant flow through the study. Note: K10 = Kessler Psychological Distress; LTSAE = Learn the Signs Act Early

**Fig. 2 Fig2:**
[figure not shown]
SPIRIT flow diagram of the WMG-E study. Note: K10 = Kessler Psychological Distress; LTSAE = Learn the Signs Act Early

#### Groups

##### Intervention group

Participants allocated to the intervention group whose responses to the Time 1 questionnaires indicate mental health, psychosocial, and/or developmental risks will receive an immediate message on the device that they used to complete the questionnaires. The message will suggest that they might require additional assessment/support and will recommend that they seek relevant local services. In the intervention group, the participant’s results will be emailed to a service navigator who will then contact participants via telephone and direct them to relevant care pathways depending on their identified needs. This might include, for example, further assessments and/or referral pathways as deemed appropriate. The service navigator will initially attempt to contact participants four times (two telephone calls and two emails, contact attempts will be tracked on an excel spreadsheet). If participants do not engage with the service navigator they will be considered as drop-outs from the RCT.

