Families with lower level risks will be connected with local services and might also be provided with information on online resources (e.g., free to access online parenting programs such as ParentWorks [19] or Movember Family Man [20]) or therapist-assisted interventions (e.g., online or in-person Parent-Child Interaction Therapy [21]). For families who are at high risk, in addition to receiving resources and linkages to services as mentioned above, they will receive in-person assessments (through a KIDS-Connect hub [22] with capacity to reach families at homes or other community facilities) to determine the complexity of health needs followed by appropriate referrals and a ‘warm hand-over’ (i.e., directly linking patients to services in a supportive manner) to recommended services. The duration of in-person (or digital as indicated in extreme circumstances) assessments will depend on the needs identified by the WMG-E, however, these assessments generally range from 30 to 60 min [22]. Once the in-person assessment is completed and families are linked with recommended services, the type and duration of services they receive will depend on their needs. For example, families with psychological needs may receive ten 60-min sessions with a psychologist while families with unmet psychosocial needs who access services such as Uniting (community service agency) [22, 23] may receive 2–3 sessions targeted at addressing psychosocial needs. Furthermore, these families will receive follow-up support by the navigator to ensure engagement with recommended services and continuity of care. Follow-ups will occur fortnightly via telephone for a duration of 10 to 20 min.

We hypothesise that in the first 6 months, the intervention group will have better access and engagement with services due to this group not only getting linked up with services but also continuity of care through the service navigator to ensure the uptake of recommended services. Further we hypothesize that, families in the intervention group that are connected with services will also show a significantly greater increase in wellbeing relative to the control group, at the 12 month follow up. This is because, via the service navigator, they will have assistance in connecting with services and ongoing monitoring and support to ensure that their needs are being met.

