#### Procedure

##### Recruitment

Families attending child and family health services, refugee health services, supported playgroups, parenting groups, NGO services, GP clinics, special paediatric clinics, or Child and Family Health Nurse services in Murrumbidgee LHD and Fairfield LGA will be informed about the study by their service provider. They will also be provided with a quick response (QR) code with a hyperlink to the WMG-E app which they can access using tablet devices provided by the service they are attending or using a personal smartphone. Families will be excluded from the research if they are allocated to the control group but are in “acute crisis” based on their questionnaire responses (i.e., K10 > 25 and/or risk of homelessness, domestic violence, loss of electricity, or no food). These families will automatically be considered RCT dropouts and will be contacted by a researcher who will assist them in engaging with services.

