##### Care-as-usual group

Participants allocated to the CaU will complete Time 1 questionnaires and, if indicated, will also receive a message that their responses to the questionnaires suggest developmental, psychological, and/or psychosocial risk and to seek assistance from local services/organisations. They will then be invited via email to complete Time 2 and Time 3 questionnaires. The control group will not have a service navigator and will not receive continuity of care and support.

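### Not engaging with the navigator is recorded as dropping out of the trial, a post-randomisation exclusion on adherence that can act in the intervention arm only

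*Protocol article*

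**What the plan says.** Under Randomisation, allocation follows consent and baseline: "Upon completion of the consent forms and Time 1 questionnaires, families will be randomised to either the intervention or CaU group". The ratio is 1:1. Navigator contact therefore comes after allocation.

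Under Intervention group, "The service navigator will initially attempt to contact participants four times", by two calls and two emails. The next sentence sets the consequence: "If participants do not engage with the service navigator they will be considered as drop-outs from the RCT".

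Under Care-as-usual group there is no counterpart: "The control group will not have a service navigator and will not receive continuity of care and support". Of the controls' follow-up it says only: "They will then be invited via email to complete Time 2 and Time 3 questionnaires".

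The hypotheses, under Randomised controlled trial, predict that at 12 months "families in the intervention group that are connected with services will also show a significantly greater increase in wellbeing relative to the control group". The Discussion states the same expectation for intervention families with no condition on being connected. The models under Statistical analysis use time, group and their interaction, with no term or subset for connected families.

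The control group is itself reduced after allocation. Under Recruitment: "Families will be excluded from the research if they are allocated to the control group but are in “acute crisis” based on their questionnaire responses".

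**The concern.** Failing to take up the offered navigator is non-adherence. It is one of the ways in which a navigator service can fail, and a trial of offering that service should count it. The article turns it into a trial exit. Because the rule can act in one arm only, the intervention families who remain are selected by their own behaviour after randomisation, and the controls are not.

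The powered outcome is service utilisation. Willingness to engage with someone whose job is to link families to services is plausibly related to using services, so the selection may well be informative. It is not the same thing as the outcome, which is self-reported attendance at listed services.

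Follow-up is also at stake. If families classed as drop-outs are not sent the Time 2 and Time 3 questionnaires, their outcomes are never collected, and no later choice of analysis set can recover them.

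The wording of the wellbeing hypothesis raises a related question: does the 12-month comparison concern everyone allocated to the intervention, or a subgroup formed after allocation?

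**Working it through.** **The plan's own figure.** Inputs from Sample size calculations: 244 families (122 per arm), 30% versus 60%, 5% significance (two-sided assumed). With pooled variance under the null, z = [0.30 − 1.96 × √(2 × 0.45 × 0.55 / 122)] / √[(0.21 + 0.24) / 122] = (0.300 − 0.125) / 0.0607 = 2.88, so power is 99.8%. This agrees with the stated figure of more than 99%.

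**Bias from the rule under a true null.** From the plan: 30% use in both arms, 150 per arm, and a 5% allowance covering non-adherence, partial adherence and dropout together. Assumed, because the article gives no figures: the non-engaging share q (other than 5%) and service use among non-engagers, p_n. If the whole intervention arm has 30% use, those retained have

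p_retained = (0.30 − q × p_n) / (1 − q).

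For q = 20% and p_n = 15%: (0.30 − 0.03) / 0.80 = 33.75%, a spurious 3.8 points. The false-positive rate uses a two-sided 5% two-proportion test with 150(1 − q) retained intervention families against 150 controls.

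| q | p_n | Retained use | Spurious difference | False-positive rate |
|---|---|---|---|---|
| 5% | 0% | 31.6% | +1.6 points | 6.0% |
| 5% | 15% | 30.8% | +0.8 | 5.3% |
| 20% | 15% | 33.8% | +3.8 | 10.2% |
| 30% | 15% | 36.4% | +6.4 | 19.2% |
| 40% | 15% | 40.0% | +10.0 | 35.6% |
| 20% | 20% | 32.5% | +2.5 | 7.3% |
| 40% | 20% | 36.7% | +6.7 | 19.0% |
| 20% or 40% | 30% | 30.0% | 0 | 5.0% |
| 20% | 40% | 27.5% | −2.5 | 7.3% |

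**Can the trial afford to keep these families?** Suppose non-engagers stay in the intervention arm and use services at 30%, while engagers reach 60%. Use in the arm is 0.60(1 − q) + 0.30q. With 150 per arm:

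| q | Intervention-arm use | Power |
|---|---|---|
| 5% | 58.5% | 99.9% |
| 20% | 54% | 99.0% |
| 30% | 51% | 96.3% |
| 40% | 48% | 89.6% |

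**The wellbeing hypothesis.** Set side by side, the hypotheses restrict the intervention side to connected families, the Discussion does not, and the model compares by group. A simulation with no effect in either arm shows why the difference matters. Connected was represented by baseline K10 of 20 or more, with K10 mean 17 to 21, SD 7 and baseline-to-follow-up correlation 0.5 to 0.7, all assumed. By regression to the mean alone, the connected subset improved by 1.5 to 3.8 K10 points more than an unreduced control group, and by 2.5 to 4.6 more than controls with K10 of 25 or below. Its follow-up K10 level was nevertheless 4.1 to 6.5 points worse than that of those reduced controls. Change and level point in opposite directions, so the restricted wording fixes no single direction of bias.

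**The case against.** The strongest case on the other side has four parts.

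*The direction is not shown.* A reader might infer that the rule must favour the intervention. The documents do not support that, because they say nothing about service use among non-engagers. If these are families managing well through services they found themselves, the sign reverses. This stands: the direction is expected, not proven.

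*The size may be small.* The plan allows 5% for non-adherence and dropout together. At that level the distortion is 0.8 points with 15% use among non-engagers, and 1.6 points even with no use at all, against a planned difference of 30 points. This also stands. The 4-to-10-point range needs 20% to 40% non-engagement, which is the reviewer's assumption. The article itself does not hold firmly to 5%, since going from 244 to 300 would absorb a loss of 1 − 244/300 = 18.7%.

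*The article does not say that drop-outs leave the analysis.* A reader might infer that non-engagers vanish from the results. The text does not go that far: the Assessments section sets no engagement condition on the three questionnaires, and a separate analysis plan may define the analysis set. This tempers the point but does not remove it. The article calls these families drop-outs from the trial and nowhere says that they are still followed.

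*The connected comparison is not a planned analysis.* A reader might infer that connected families will be tested against the whole control group. Neither part is supported. The model and the Discussion compare by group, and acute-crisis families are removed from the control group after allocation. What remains is an inconsistency of wording.

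**Conclusion.** The point holds for the drop-out rule. As written, it makes non-adherence a trial exit after randomisation, in one arm only, and on a characteristic plausibly related to the powered outcome. Following it would break the randomised comparison of service utilisation whichever way the bias runs.

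The size cannot be fixed from the documents. It is under 2 points at 5% non-engagement if non-engagers use services less than or as much as others. At 20% to 40% non-engagement with 15% use it is 3.8 to 10 points, with a false-positive rate of roughly 10% to 36%. It is zero if non-engagers use services at the same rate as engagers, and negative if they use them more.

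The hypothesis wording is a lesser matter: the hypotheses, the Discussion and the model must be reconciled. The rule should be corrected before follow-up begins, because uncollected outcomes cannot be recovered and the correction is cheap.

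**What to change.** - In the Intervention group section, record failure to engage with the navigator as non-adherence, and keep drop-out for withdrawal or loss to follow-up.
- State that all randomised families are invited to Time 2 and Time 3 whether or not they engaged, and are analysed in the arm to which they were allocated.
- State the 12-month wellbeing hypothesis for all families randomised to intervention versus control, in agreement with the Discussion and the model, and say how the acute-crisis removals from the control group bear on who is compared.
- Keep any analysis of engaged or connected families secondary and supportive. If a complier-average estimate is used, define compliance as navigator engagement and state the exclusion restriction, namely that allocation has no effect on families who do not engage. Defining compliance as connection to services would be harder to defend, because the navigator's contact may act directly and the Limitations section concedes that navigator and service effects are hard to separate.

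The cost is protocol wording and questionnaire emails to non-engagers. The effect estimate may be smaller. On the plan's 30% and 60% rates, with non-engagers at 30%, power at 150 per arm is still 89.6% with 40% non-engagement.

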##### Care-as-usual group

Participants allocated to the CaU will complete Time 1 questionnaires and, if indicated, will also receive a message that their responses to the questionnaires suggest developmental, psychological, and/or psychosocial risk and to seek assistance from local services/organisations. They will then be invited via email to complete Time 2 and Time 3 questionnaires. The control group will not have a service navigator and will not receive continuity of care and support.

#### Measures

The following measures have been incorporated into the WMG-E weblink to identify mental health, psychosocial, and development risks.

##### Parent mental Health

Parent psychological distress will be assessed using the Kessler Psychological Distress (K10) scale [18] – a ten-item measure. Using a five-point Likert scale, parents are required to indicate how often they have experienced symptoms of depression and anxiety as well as somatic symptoms over the past 4 weeks. One indicates ‘none of the time’ and five, ‘all of the time’. Each item score is combined to calculate the total score. Scores of 20 to 24 (inclusive) indicate mild psychological distress, 25 to 29 (inclusive) indicate moderate psychological distress, and 30 to 50 (inclusive) indicate severe psychological distress. The K-10 has good validity and reliability in various settings and populations [26–28].

##### Parent psychosocial needs

Parent psychosocial needs will be assessed using the WE CARE questionnaire [17]. The questionnaire consists of six (yes/no) items querying psychosocial needs: childcare, employment, homelessness, food security, education, and utilities. The measure also includes follow-up questions that appear if participants indicate “yes” to any of the six items. These items will be summed up to create a score out of 6. These follow-up questionnaires require participants to answer on a three-point scale (yes, no, or maybe later), whether they require additional support for addressing their unmet psychosocial need/s. The measure has good psychometric properties, including excellent test-retest reliability (r. = 0.92) [17].

##### Developmental risk

Developmental risk will be assessed using the appropriate Learn the Signs Act Early (LTSAE) questionnaire for their age [11]. The LTSAE is a short developmental surveillance questionnaire for children aged 2 months to 5 years that includes eight ‘red flag’ questions concerning the development of social and emotional, language/communication, cognitive, and movement/physical. The caregiver is asked to indicate whether their child engages in each of the developmental behaviours by indicating “yes”, “no” or “not sure”. The items will be summed up to create a score out of 8.

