##### Statistical analysis

A multilevel models estimated by restricted maximum likelihood (REML) with logit link function will be used to model service utilisation over the 3 time points. The main predictors of interest will be time, group and a time by group interaction which will compare service utilization between the groups at each time point. The analysis will be adjusted for the caregivers, socioeconomic status, and the main language spoken in the home.

A multilevel model estimated by restricted maximum likelihood (REML) with identity link function will be used to model the K10, WE CARE and LTSAE totals. The main predictors of interest are time, group and time by group interaction. The analysis will be adjusted for the caregivers, socioeconomic status, and the main language spoken in the home.

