## Discussion

Families from disadvantaged backgrounds face a fragmented health system with financial, social, and structural barriers. Even when services are available, engagement and access to services are compounded by cultural and linguistic barriers as well as geographic challenges. These are exacerbated by the pandemic and the consequent impact on in-person services.

This study will address these challenges by testing the WMG-E web-app as a digital navigation tool to engage parents at home or through opportunistic contacts with health, early childhood education or other community/social care services. Extending earlier research using WMG-E to engage parents in developmental monitoring [35], this study will include parental mental health and psychosocial needs, alongside child developmental needs. Thus, this study will test the acceptability, effectiveness, and cost-effectiveness of WMG-E for families of children aged 6 months to 3 years (inclusive) in a predominantly CALD community and a regional/rural community to increase engagement of families with services and better identification of their needs.

Furthermore, this study will specifically evaluate whether a service navigator will increase family wellbeing by facilitating access to relevant services. Families in the intervention group are expected to experience significantly improved parental mental health, psychosocial wellbeing, and development outcomes compared to the control group. By targeting CALD and rural/regional communities, we will demonstrate the feasibility of the WMG-E for the most vulnerable and disadvantaged families. Following this, the online platform will be ready for national implementation with potential for international adaptation.

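### The LTSAE total comes from a checklist that changes with the child's age, but its model over three visits omits child age: the time effect is not developmental change, and the arm contrast at a visit may lose precision

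*Protocol article*

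**What the plan says.** Under Measures, Developmental risk, the protocol article states: "Developmental risk will be assessed using the appropriate Learn the Signs Act Early (LTSAE) questionnaire for their age". The form has eight red-flag questions answered yes, no or not sure, and the scoring is: "The items will be summed up to create a score out of 8". No age referencing of the total is described.

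Under Participants, children may be 6 months to 3 years old at entry. Under Assessments, the questionnaires are repeated at nominal 6 and 12 months. The baseline demographic form "will include the child’s date of birth, the child’s gender, whether the child was born premature", so age at every visit can be computed.

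Under Statistical analysis, a multilevel model estimated by REML with "identity link function will be used to model the K10, WE CARE and LTSAE totals". Time, group and their interaction are the predictors of interest. The covariates are then fixed: "The analysis will be adjusted for the caregivers, socioeconomic status, and the main language spoken in the home". Child age and the LTSAE form are not listed.

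The Discussion expects intervention families to show "significantly improved parental mental health, psychosocial wellbeing, and development outcomes compared to the control group".

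**The concern.** The K10 and WE CARE are described as fixed sets of items, so a total means the same thing at each visit. The LTSAE total does not have this property. Age decides which eight questions are asked. Across a 30-month entry range, children at the same visit answer different forms, and a child followed for a year will generally move from one form to another. One analysis sentence treats all three totals alike.

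Two things are at stake. First, the time coefficient, which the article names as of interest, combines ageing, a change of questions and any real change in risk. This matters because one secondary objective concerns how well the platform identifies and addresses developmental needs. Both arms use the platform, so no randomised contrast isolates it, and the change over time is the obvious figure to reach for. Second, if flag counts vary with age or form, that variation stays in the residual of the arm comparison at a visit, although the variable that would remove it is already collected.

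**Working it through.** **The plan's own figure.** The only design calculation concerns service utilisation: 244 families, 30% against 60%, 5% significance (two-sided assumed). With 122 per arm and the pooled-variance formula, z = [0.30 × √122 − 1.960 × √(2 × 0.45 × 0.55)] / √(0.30 × 0.70 + 0.60 × 0.40) = (3.314 − 1.379) / 0.671 = 2.88. Power is 0.998, so the stated figure of more than 99% reproduces. It says nothing about the LTSAE, for which the article gives no standard deviation, effect size or relation to age. What follows is therefore a range under stated assumptions.

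**Step 1: arm contrast at one visit.** If age or form explains a share R² of the variance of the total, adjustment multiplies the standard error by √(1 − R²). With 150 per arm and 80% power, the detectable difference is (1.960 + 0.842) × √(2/150) × √(1 − R²) standard deviations. This takes complete data; dropout would raise every value in the last column.

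| R² (assumed) | √(1 − R²) | Interval narrower by | Detectable difference |
|---|---|---|---|
| 0% | 1.000 | 0% | 0.323 SD |
| 5% | 0.975 | 2.5% | 0.315 SD |
| 10% | 0.949 | 5.1% | 0.307 SD |
| 20% | 0.894 | 10.6% | 0.289 SD |

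**Step 2: between-arm difference in change.** Suppose the expected total is linear in age with slope b per month. Over 12 months every child's expected total then moves by 12b, whatever the entry age. Age contributes no between-child variance to the change, so adjusting for it gains nothing. A random-intercept REML simulation (300 children, three visits, complete data, linear age effect explaining 5%, 10% or 20% of the variance) agrees: the time-by-group standard error was unchanged (ratio 1.000 each time), while the single-visit contrast narrowed (ratios 0.97, 0.95 and 0.90).

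**Step 3: bias and drift.** A second simulation used 4,000 trials of 300 children, entry age uniform from 6 to 36 months, child and residual standard deviations of 0.7 each, and no treatment effect. The adjusted analysis used a cubic in age.

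| Assumed age effect | SE ratio, change to 12 months | SE ratio, 12-month contrast | Control-arm drift |
|---|---|---|---|
| None | 1.00 | 1.00 | 0.00 |
| Linear, 0.04 points per month | 1.00 | 0.95 | 0.48 |
| Strongly curved, peak 1.2 points at 24 months | 0.80 | 0.91 | −0.07 |

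Ratios are adjusted over unadjusted. The mean arm contrast was within 0.005 of the true zero in every scenario, with or without age. The linear drift is 12 × 0.04 = 0.48 points: a shift in the raw total with no intervention effect at all. These age effects are illustrations, not estimates.

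**The case against.** The strongest reply is that the randomised comparison is sound as it stands. Both arms receive the same forms at the same ages, and omitting a prognostic baseline variable does not bias a randomised contrast. The article's outcome hypotheses are between-arm: the Discussion compares with the control group, and the wellbeing hypothesis is also relative to control. The outcome is labelled developmental risk and counts red flags on an age-appropriate form, so it is meant to ask different questions at different ages. The documents do not show that flag rates differ by form. The LTSAE does not size the trial, and details of age terms are often left to an analysis plan.

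Most of this stands. A reader might infer that leaving age out biases the treatment effect; the documents do not support that, and Step 3 shows no bias. A reader might also infer that precision is certainly lost, or that adjustment is worth a fixed number of extra families. That is not supported either: no age relation is given, zero is a possible value, and the single-visit factor does not carry over to the difference in change.

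Two things remain. The article does not defer the choice: it states the outcome, the link, the effects of interest and a covariate list. The phrase about caregivers may have lost a word, but nothing in it points to child age. And the article names time as a predictor of interest for a total whose items change, with no caution on how to read it.

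**Conclusion.** The point holds as a matter of interpretation and as a free improvement, not as a flaw in the treatment comparison. The LTSAE time coefficient cannot be read as developmental change. The between-arm contrast at each visit and the time-by-group effect stay unbiased through randomisation.

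The precision at stake is conditional. For a single-visit contrast, which is how the article describes the use of the interaction in its service-utilisation model, the interval narrows by 0% to about 11% if age or form explains 0% to 20% of the variance. For the between-arm difference in change, the gain is nil under a linear age effect and appears only if the effect is curved. All these sizes rest on assumed age effects, since the documents supply none. A reader might infer that the article promises a finding of improvement from baseline; it does not, and the caution here concerns how a named coefficient could be used.

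**What to change.** In Statistical analysis, make three changes for the LTSAE outcome:

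- Add child age, computed from the collected date of birth and entered flexibly (for example as a spline or age bands), or the LTSAE form used.
- State that conclusions about development rest on the between-arm contrasts at Time 2 and Time 3.
- State that change in the raw total over time is not to be read as developmental change. This sentence is needed even with age in the model, because a covariate does not turn different questions into one scale.

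Prematurity need not be added; nothing in the documents argues for it here. The cost is one model term and two sentences, with no new data, visits or participants. The choice should be fixed before outcome data are examined by arm.
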